**Fig. 1 Fig1:**
[figure not shown]
CONSORT (Consolidated Standards of Reporting Trials) flowchart for the self-management randomized controlled trial

The study design will include a baseline collection period, followed by sequential, individual randomization to control or intervention. The intervention group and control group will be continually recruited and exposed to the intervention plus standard care and/or standard care with baseline and follow-up observations collected (see “Participant timeline {13}”) until target numbers are achieved (see sample size {14}). All participants will be asked to sign informed consent before the commencement of the study.

This is a pragmatic trial for the following reasons:Our systematic review published in the Journal of Advanced Nursing (2021), provides evidence that self-management programs are effective for adolescents. We have been using the Flinders Program™ clinically for over 5 years with success in demonstrated effectiveness in self-management capacity. What is less well understood is how effective self-management programs remain over time, given the rapid bio-neuro-psychosocial development during adolescence. This study has the capacity to demonstrate duration of effect with 12-month follow-up planned.Given the challenge of recruiting and retaining adolescents in health service research from the clinical experience of the research team and the clear clinical need to intervene [36], the combination of stepped intervention with assessment of duration of effect and guidance on booster sessions appears the more appropriate methodological option.

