### Who will take informed consent? {26a}

The principal investigator retains the overall responsibility for ensuring that consent has been obtained from participants in the correct manner. The principal investigator may delegate this responsibility to a member of the research team with the appropriate training, experience, and knowledge to explain fully to potential research participants the implications of participating in the trial. Trial data will be collected from potential trial participants by a member of the research team via telehealth, in person or by phone or email if other methods are unobtainable. Following the confirmation of the participant eligibility and the participant has had time to review the study information provided, consent will be sought. Informed consent (see Additional File 2), where possible, will be collected in person by a member of the research team prior to the collection of baseline data. All participants will be assigned a study identification code linked to their personal information. All trial data will be recorded and stored in a separate password-protected computer within the Department of Adolescent Medicine at The Children’s Hospital at Westmead and accessible only by the primary research investigators (JG, KS) and any research staff associated with the study. Signed consent forms, questionnaires, and other paper data including the master list linking the personal information of participants and personal ID numbers will be secured in a separate locked cabinet in the Department of Adolescent Medicine and accessible only by the primary research investigators.

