#### Initial assessment of self-management

All participants complete the PIH Scale, a self-rated questionnaire, based on their individual perception of their self-management capabilities. The participant rates their answers on a 9-point scale ranging from never (0) to always (8). This is followed by the C&R interview which is administered by a health professional and uses open-ended cue questions to explore in more detail the patients’ responses to the same 12 questions in the PIH scale. This enables the identification of the participant’s understanding and knowledge, as well as the barriers and enablers to self-management. The C&R interview is scored using the same 9-point scale as the PIH scale by a member of the research team trained in the Flinders Program, and the scores are compared and discussed with the participant. Scores of 4 or below (out of a total maximum score of 12) and discrepancies of 3 or more on either side of 4 rated by the participant or the health professional are flagged as issues requiring further discussion and are addressed in the care plan [46]. The health professional uses open-ended questions to identify the participant’s main problems, impact of chronic illness, and feelings to foster collaboration and partnership. This leads to the development of agreed short- to medium-term goals (3 to 6 months) to address the identified problems. These target issues are then integrated into the negotiated individualized care plan which is reviewed at follow-up [46]. The participant is provided with a copy of the care plan which is either sent to their personal email address or posted in the mail directly to them. A clinic letter is sent to the referring specialist and parents/carers indicating that the adolescent has commenced a self-management program which is directed at increasing autonomy and goal setting and does not contain any details of the intervention.

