#### Follow-up data collection

Adherence to prescribed treatment regimenBaseline observations will be collected from both the waitlist control group and the intervention group before randomization. Potential participants in the intervention group will be contacted via phone by a member of the research team. Follow-up of participants in the intervention group will be undertaken by a member of the research team via phone or telehealth (depending on the young person’s preference) at 3, 6, and 12 months to follow-up on adherence to the prescribed treatment post intervention. Participants who do not respond to 3 attempts to contact them at any time point will be treated as missing data.

Information from the participants will be obtained by completing the PIH scale via a semi-structured interview. Subsequently, participants allocated to the wait list control group will be contacted by phone by a member of the research team and provided with a self-management information brochure, with no further contact from the research team. At 6 months, participants in the waitlist control group will be contacted by phone by a member of the research team and invited to participate in the intervention as described for the initial intervention group.(b)Markers of illness control and unplanned hospital visits

The research team will obtain standard measures of illness control for all participants who have been recruited into the study and who have consented to clinical information being obtained for research purposes. The control of chronic illness is the best quantitative measure of therapy adherence that is available. This will be undertaken by way of the research team extracting information from the electronic medical records (EMR) and the young person’s primary physician contacted for further information. Data on unplanned hospital visits will be retrieved by the research team from EMR and/or accessed through the young person’s My Health Record if available.

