#### Kessler Psychological Distress Scale (K10)

The Kessler Psychological Distress Scale (K10) is a well-recognized instrument which has demonstrated content and construct validity for measuring non-specific symptoms of psychological distress including behavioral, emotional, cognitive, and psychophysiological manifestations [62]. Initially developed for the US National Health Interview Survey (NHIS), the 10-item scale (K10) has been extensively used in both clinical and general populations including adolescents, and used in a variety of cultural and sociodemographic backgrounds [63]. The K10 scale measures the frequency of symptoms (nervousness, hopelessness, sadness, worthlessness, and fatigue) experienced in the past month using a 5-point Likert scale ranging from none of the time (1) to all of the time (5), producing a total score range of 10–50 with higher scores correlating to more distress [62]. A study conducted by Sampasa-Kanyinga et al. found that the K10 scale has satisfactory psychometric properties for use as a measure of non-specific psychological distress with high internal consistency (0.84) [64].

Adolescents with a chronic condition are more likely to develop psychiatric and behavioral disorders including depression and low self-esteem than their healthy counterparts. Thus, the K10 scale was chosen as it presents as a useful tool in identifying psychological symptoms in participants, and from our previous clinical experience in working with adolescent populations, the accessibility and simplicity of the K10 scale makes it an ideal instrument to use within this population group. [65]. It is not a diagnostic tool.

The mean and standard deviation of the scores for the outcome measures described above will be described in each group and at each time point, following randomization at baseline, 3 months, and 12 months.

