## Assignment of interventions: allocation

### Sequence generation {16a}

Following formal consent, the participants will be randomized. Successively, baseline data collection and measures of illness control will be collected for both the control and intervention groups. Randomization will be stratified by disease condition (diabetes, CF, renal, inflammatory bowel disease, other) and will use permuted blocks to maintain balance.

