## Assignment of interventions: blinding

### Who will be blinded {17a}

This trial is not blinded. As with all studies of this type of intervention, it is not possible to blind trial participants or the researchers who must know what group the participant is assigned to. To avoid potential bias during the statistical analysis of the trial, the data analyst will be blinded until the entire analysis has been completed.

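### The sequence-generation section places baseline after randomization, against two other sections; in this open trial that would let self-reported baselines be given with the arm known

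*Protocol article*

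**What the plan says.** Sequence generation {16a} gives the order as consent, randomization, baseline: "Following formal consent, the participants will be randomized", and then "Successively, baseline data collection and measures of illness control will be collected for both the control and intervention groups".

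Two other places give the reverse. Follow-up data collection: "observations will be collected from both the waitlist control group and the intervention group before randomization". Trial design {8}, in the text after Fig. 1: "The study design will include a baseline collection period, followed by sequential, individual randomization to control or intervention".

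Two further statements do not settle the matter. The closing paragraph on the K10 describes questionnaire scores "following randomization at baseline, 3 months, and 12 months", which leans towards the {16a} order but can be read either way. The consent section {26a} says that consent "will be collected in person by a member of the research team prior to the collection of baseline data", which fits both orders.

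On blinding, section {17a} says "it is not possible to blind trial participants or the researchers who must know what group the participant is assigned to"; only the data analyst is blinded.

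**The concern.** A baseline measured before allocation cannot be influenced by allocation. A baseline measured afterwards in an open trial can be. Under the {16a} order, an adolescent would rate self-management, quality of life, time management and distress knowing whether the program starts now or in 6 months. Disappointment or expectation could then move the baseline in one arm and not in the other.

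The same order bears on the primary outcome by a narrower route. Response is judged against baseline, and the research team, which knows the arm, extracts the markers from the medical record. If baseline is fixed after allocation, so is the choice of which dated value serves as baseline. For epilepsy (Table 1) the improvement criterion is set individually, and for conditions not in Table 1 it is agreed with the referring team (Measures of illness control). Nothing in the {16a} order requires either to be fixed before the arm is known.

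**Working it through.** **1. The orders side by side**

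| Place in the protocol article | Order stated |
|---|---|
| Trial design {8}, after Fig. 1 | baseline, then randomization |
| Follow-up data collection | baseline, then randomization |
| Sequence generation {16a} | consent, randomization, then baseline |
| K10, closing paragraph | ambiguous |
| Consent {26a} | consent, then baseline; silent on randomization |

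The first two rows cannot both hold with the third. No section says that the allocation is withheld until baseline is complete. The sealed envelopes in {16b} protect enrolment, but not a baseline taken after the envelope is opened.

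**2. Which baselines depend on the participant's own report**

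PIH, PedsQL, TMQ and K10 are all self-reported and all taken at baseline (section {18a}). For the PIH there is an added ambiguity. Under Initial assessment of self-management, "All participants complete the PIH Scale, a self-rated questionnaire, based on their individual perception of their self-management capabilities", as the opening step of the program's assessment. Table 2 puts both the PIH and program delivery in the intervention arm's baseline column. The article does not say whether the trial baseline PIH is that one or a separate one.

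**3. How a shifted baseline would reach a comparison**

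Let d be the difference between arms (intervention minus control) in mean baseline score that is caused by knowing the arm. Assume that follow-up scores are not changed by it. Let b be the slope of follow-up on baseline.

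- Follow-up scores compared directly: bias = 0.
- Follow-up adjusted for baseline: bias = −b × d, a fraction of d when b is between 0 and 1.
- Change from baseline: bias = −d.

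The article does not commit to one of these for the questionnaires. Section {20a} names two-sample tests between randomized groups and models for repeated observations. The K10 paragraph describes means and standard deviations per group and time point. The PIH section describes the percentage at or below 4 at each follow-up. The documents give no value for d or b.

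**4. The primary outcome**

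For cystic fibrosis, diabetes, inflammatory bowel disease, kidney disease and asthma, Table 1 fixes the marker and the threshold, and the values come from the medical record. What stays open under the {16a} order is the dated value used as baseline, and the criterion for epilepsy and unlisted conditions.

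**5. Sample size**

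The stated 27 per group reproduces: 15% against 50%, two-sided 5%, uncorrected chi-square, gives 27 per group with approximate power 80.2%. Nothing in that calculation depends on the order of baseline and randomization.

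**The case against.** The strongest reply is that the protocol's intent is clear. Two sections, one of them the design section, put baseline first; only one loosely worded paragraph says otherwise, and Figs. 1 and 2, not available here, may show the order. This stands in part: the contradiction does not show that anyone meant to take baseline after allocation, or did so. But {16a} is where staff would look for the order of steps around allocation, and a figure would not remove the conflicting sentence.

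Four stronger readings are tempting, and the documents do not support them.

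- *That every between-arm comparison is biased.* A recorded HbA1c or FEV1 does not move because a participant learns the arm, and a plain comparison of follow-up questionnaire scores does not use baseline.
- *That the bias has a known size, such as 0.1 to 0.3 SD.* Such a range would be an assumption about d handed back as a result.
- *That a participant lost between allocation and baseline leaves nothing to analyse.* Sections {14} and {20c} allow clinical outcomes of those who withdraw to be taken from records. Only the questionnaires would be lost.
- *That discussing PIH scores with the nurse contaminates the baseline PIH.* The self-rating comes first, then the interview, then the discussion, so the discussion cannot alter a score already given. The open question is only whether the arm is known when the PIH is completed.

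**Conclusion.** The contradiction is certain; the bias is conditional. It arises only if the {16a} order is followed. It then bears mainly on PIH, PedsQL, TMQ and K10, to the extent that they are analysed as change from baseline (shift carried in full) or adjusted for baseline (carried in part). The primary outcome is exposed only through the choice of dated baseline value and the individually set improvement criteria. Neither effect can be sized from the documents. The point should still be corrected, because the open allocation gives a credible route to bias and the remedy is nearly free. It does not undermine the primary analysis.

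**What to change.** Correct Sequence generation {16a} to match Follow-up data collection and Trial design {8}, and reword the K10 paragraph so that baseline is not described as following randomization. State one order:

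1. Consent.
2. All baseline questionnaires, including the PIH, and the dated baseline marker value entered in REDCap, together with any individually negotiated improvement criterion.
3. Opening of the envelope.

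State that the trial baseline PIH is the one completed before allocation, not the one from the first Flinders session.

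Trial status says that recruitment began in December 2021. For participants already enrolled, establish from REDCap timestamps which order was followed and report it by arm.

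The cost is a wording correction, a fixed order of steps at entry and a check of timestamps. No new measures and no change to the sample size are needed. At most the PIH is completed a second time, if the program needs its own at the first session.

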### Concealment mechanism {16b}

Assignment envelopes will be opaque, sealed, sequentially numbered, and opened in the correct order when the intervention is assigned. In accordance with the CONSORT statement (item 10), the envelopes will be prepared and opened by a clinician who is separate from the recruitment of participants [67].

### Implementation {16c}

The random sequence will be prepared by a statistician with no involvement in the trial using computer-generated random numbers. Participants will be sequentially randomized to one of two groups: the intervention group (Flinders Program™) or the control group (standard care for 6 months) before crossing over until all participants have been exposed to the intervention by the end of the trial. Additionally, data will be collected at each step.

## Assignment of interventions: blinding

### Who will be blinded {17a}

This trial is not blinded. As with all studies of this type of intervention, it is not possible to blind trial participants or the researchers who must know what group the participant is assigned to. To avoid potential bias during the statistical analysis of the trial, the data analyst will be blinded until the entire analysis has been completed.

### Procedure for unblinding if needed {17b}

Not applicable to this study.

## Data collection and management

### Plans for assessment and collection of outcomes {18a}

Patient demographic data will be collected at baseline (see Additional file 3). All data collection questionnaires are programmed in Research Electronic Data Capture (REDCap) and include Partners in Health (PIH) Scale, collected at baseline, 3, 6, and 12 months follow-up. Paediatric Quality of Life Inventory (PedsQL) version 4.0 (Teenage Report); Time Management Questionnaire; Kessler Psychological Distress Scale (K10) collected at baseline, 3 months, and 12 months follow-up. Additional data on makers of illness control and unplanned hospital admissions and emergency department visits will be obtained from the EMR at baseline, 3, 6, and 12 months follow-up. Data questionnaire on feasibility and acceptability will be collected on completion of the study at 12 months (see Additional file 4). Data will be collected and stored in REDCap a secure web-based application used for designing and managing clinical research databases. REDCap is an online data capture tool which stores data in a secure and encrypted manner on the University of Sydney server to which we have access [68]. This research data management platform is a secure web-based software platform used for the data management procedures of this trial including data collection, follow-up, and analyses. The built-in component of REDCap has been pre-prepared to accept only variables within given permissible ranges that are consistent with previous entries before going on to the next section to minimize missing values. Data collection forms pertaining to the study will also be stored in REDCap.

Prior to the commencement of the study, research staff completed the Flinders training workshop conducted over 2 days, by the lead research nurse (JG) who is an Accredited Flinders Trainer. All research staff were assessed as competent against current Flinders competency standards. The training was guided by validated manuals (Accredited Trainer: Flinders Chronic Condition Management Program Manual; The Flinders Chronic Condition Program Participant Manual) with electronic copies of all training resources and PowerPoint presentations available to ensure reproducibility and fidelity of the intervention program.

In addition to the delivery of training required for the implementation of the intervention, a self-report evaluation checklist was developed by the research team, specifically for the study, to guide each interview and to assess fidelity ensuring that all key points are covered during each consultation. The self-report checklist is completed immediately after the consultation by the health professional delivering the intervention and is emailed to the research nurse coordinator. Follow-up quality assurance checks will also be completed by the research team as part of the study after each consultation. Information around attendance, aspects of the program covered in the first and subsequent sessions, length of consultation visits, records of all face-to-face consultations and phone contact, and the development of a care plan will be recorded. The training and self-report evaluation checklist serve to minimize technical deviations from the protocol and provide reproducible results.

### Plans to promote participant retention and complete follow-up {18b}

Participants can withdraw from the study at any time. If the patient decides to withdraw from the study, data collected will be retained as outlined in the consent and the reasons for the withdrawal, if provided, will be recorded for subsequent analysis in the interpretation of results. Participants who withdraw from the study will not be replaced as the power analysis allows for attrition.

In the first 3 months, participants will receive a maximum of 3 phone calls from a member of the research team. In addition, an appointment letter is confirming the details of the next appointment is sent to the participant either electronically or sent in the mail which serves as a reminder of the next scheduled appointment to improve adherence and participation to the intervention.

### Data management {19}

Trial data will be recorded and stored in a separate password-protected computer on a secure server within the Department of Adolescent Medicine at The Children’s Hospital at Westmead and accessed only by the primary research investigators (JG, KS) and essential research staff associated with the study. Signed consent forms and other paper data including the master list linking the personal information of participants and personal ID numbers will be secured in a separate locked cabinet in the Department of Adolescent Medicine. The master list will be securely stored separately from other documents containing participant data.

All participant information collected as part of the study will be de-identified on receipt by the investigators and will be coded with participant numbers to ensure confidentiality and anonymity. Digital data collected will be stored on REDCap as described previously.

De-identified digital data will be on a password-protected database on a restricted access network drive. Only the principal investigators will have access to the participant ID number-name reference master list, and this will remain as a separated hard copy and stored separately. The lead research nurse (JG) will randomly double-check a small proportion (10 percent) of the entered data for any outliers and for accuracy.

